#### Secondary endpoints

Secondary endpoints are: (1) the number of moderate and severe postoperative complications in total, per patient and for each individual complication; (2) the occurrence of at least one of these complications on days 1, 3, 5, 7, and 28 in total and for every complication. The additional secondary endpoints include (3) days alive and free of mechanical ventilation, vasopressor therapy and renal replacement therapy, length of ICU and hospital stay at day 7 and day 28 further characterize perioperative morbidity and its socioeconomic impacts. (4) For the assessment of quality of life, an interview (personal or by telephone) based on the EQ-5D-5L™ questionnaire [23] is performed at the time point of enrollment and 6 months after surgery. Mortality is assessed 6 months after surgery. All the secondary endpoints mentioned above will be recorded at the defined time points, but will be analyzed at the end of the study.

### Intervention scheme

The intervention schemes are given in Figs. 2, 3, and 4. The schedule of events is summarized in Fig. 5.

**Fig. 5 Fig5:**
[figure not shown]
Schedule of events

### Documentation and data acquisition

Data will be obtained by a web-based eCRF. Study centers will be trained on the use of the eCRF before initiating a patient’s enrollment. To enter a patient into the iPEGASUS trial, research staff at the site will log on to a secure, web-based randomization system via a link to the respective website and complete the patient’s details to obtain a unique patient number and allocation to a treatment group. The local main investigator (LMI) will then be informed about the patient’s enrollment. For correct patient data follow-up only the LMI will set up a list with the possibility to retrace the patient’s history. Personalized data will be handled by the LMI according to Good Clinical Practice (GCP) requirements. In contrast, data in the eCRF, visible only for the coordinating investigators, will be completely anonymized and not be re-traceable. Data management of the eCRF will be performed by a company specialized in full service study data management (MedSurv GmbH, Nidderau, Germany).

To reduce bias resulting from lack of experience in the use of the protocol, the first two enrolled patients of each center (one allocated to the control group, one allocated to the intervention group) will be withdrawn from the study. Source data verification, quality assurance and monitoring of data during on-site monitoring visits will be performed by the dedicated monitoring team with appropriate frequency according to center performance. The monitoring team will be provided by the Hamburg-Eppendorf University Medical Center.

#### Methods against bias

Due to the nature of the intervention, blinding to all types of staff involved in the study is not possible. Primary and secondary outcome parameters will be assessed by a local investigator, on days 1, 3, 5, 7, and on day 28, blinded to allocation. Moderate and severe complications will additionally be verified by the LMI or a designee. Source data verification will be performed by the monitors by regular on-site monitoring visits. To minimize bias provoked by learning principles of goal-directed therapy in the past, and thereby influencing control group treatment, predominately hospitals without prior regular use of cardiac output monitoring in the respective procedures were selected. Further, the inclusion of non-university centers will allow better comparison of the study group to the broad clinical reality.

#### Compliance/rate of loss to follow-up

After enrollment of the patient’s address, telephone number, and contact information of the primary care physician, a relative of the patient will also be registered enabling us to maintain contact. If patients do not reach the goals of the inclusion criteria (time of surgery > 120 min or volume therapy > 2 l) they will be excluded from the study subsequently. Visits by a local investigator will be performed on days 1, 3, 5, 7, and 28 to assess postoperative complications necessary for primary and secondary endpoints. However, if patients are discharged from hospital to home, to a secondary hospital, or to a rehabilitation facility before day 28, final determination of all parameters relevant for the primary and the secondary endpoints will be assessed on day 28 by a structured telephone interview with the secondary hospital, the patient or the rehabilitation facility or the primary care physician. Due to the lack of subsequent examinations of the patient after day 28, loss to follow-up is unlikely. However, to reflect an unscheduled loss to follow-up an overall dropout rate of 10% is already included in the sample size calculation.

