### Study population

To be eligible for inclusion into this study (day 0), each patient must fulfill all the inclusion criteria during screening and prior to enrollment into the trial.

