#### Inclusion criteria

To ensure the presence of marked surgical trauma, open visceral, urological, and gynecological surgery are covered by this study. Expected duration of surgery must be ≥ 120 min and the requirement of volume therapy must be expected to be ≥ 2 l. Risk for any postoperative complications must be ≥ 10% as assessed preoperatively by the ACS-NSQIP (American College of Surgery – National Surgical Quality Improvement Program, www.acsnsqip.org) risk calculator [4, 18, 19].

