### Treatment of the control group

Patients in the control group will be treated according to established basic treatment goals as described in the general information on patient treatment (heart rate < 100 bpm, mean arterial pressure > 65 mmHg, SpO_2_ > 94%, and core temperature > 36 C). In the control group, no specific vasopressor is prescribed to achieve the mean arterial pressure goal and the choice of drug is at the discretion of the treating anesthesiologist. Basic anesthesiological monitoring by five-lead electrocardiogram, pulse oximetry, non-invasive blood pressure monitoring and capnography is performed in every patient. Placement of an arterial and central venous line is at the discretion of the treating clinician, as is the decision to administer fluids and catecholamines. After extubation, hemodynamic treatment in the recovery room is at the discretion of the treating anesthesiologist either by administration of fluids, catecholamines, or other drugs as required.

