### Treatment of the intervention group

The trial intervention period will commence from the induction of anesthesia until 8 h after surgery, or until discharge from the postoperative intensive or intermediate care unit. Drugs of choice are dobutamine for inotropic support and norepinephrine as a vasopressor. No other catecholamines should be used in the intervention group. Hemodynamic management is performed according to standard treatment until an arterial catheter is placed. The signal from the arterial catheter is then processed by non-calibrated pulse-contour analysis (ProAQT©; Pulsion Medical Systems, Feldkirchen, Germany) for pulse-pressure variation (PPV) and cardica index (CI) measurement. A fluid challenge will be performed by infusion of 500 ml in < 15 min. The choice of fluid in case of indicated fluid loading is determined on the basis of the recent guidelines for volume therapy [20].

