#### Primary and secondary endpoints

Baseline sample characteristics will be shown for all randomized patients treatment-wise and for pooled data. For categorical variables, category frequency counts and percentages will be shown. For continuous variables, the arithmetic mean, median, 1st and 3rd quartiles, minimum and maximum values will be presented. Follow-up data will be given in line plots allowing visual comparisons between treatment groups.

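### Randomised patients are excluded on achieved surgery time or volume, and volume depends on the assigned arm, so randomisation no longer protects the primary comparison

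*Protocol article*

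**What the plan says.** Eligibility is a preoperative judgement. Inclusion criteria reads: "Expected duration of surgery must be ≥ 120 min and the requirement of volume therapy must be expected to be ≥ 2 l". Study population adds that "each patient must fulfill all the inclusion criteria during screening and prior to enrollment into the trial". Allocation comes with enrolment: under Documentation and data acquisition, site staff "complete the patient’s details to obtain a unique patient number and allocation to a treatment group". The intervention period starts at induction of anaesthesia.

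Compliance/rate of loss to follow-up then applies similar thresholds to what actually happened. Of patients who do not reach the goals, it says: "time of surgery > 120 min or volume therapy > 2 l) they will be excluded from the study subsequently".

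Volume is managed differently in the two arms:

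- **Intervention.** The unit of loading is defined: "A fluid challenge will be performed by infusion of 500 ml in < 15 min". Algorithm 1 loads until PPV is below 12%. Algorithm 2 gives fluid when CI is under its target, for as long as PPV exceeds 12% and CI rises. Algorithm 3 gives a challenge when CI is under target and repeats it if CI rises by more than 15%.
- **Control.** Line placement is left to the treating clinician, "as is the decision to administer fluids and catecholamines".

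Methods against bias states that staff cannot be blinded. Primary analysis names no analysis set. All randomised patients are mentioned only for the baseline description: "Baseline sample characteristics will be shown for all randomized patients treatment-wise and for pooled data".

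**The concern.** Eligibility fixed before allocation cannot be influenced by the arm. A threshold on achieved volume can, because volume is part of what the two arms do differently. The same patient could fall short of 2 l in one arm and be removed, yet exceed 2 l in the other and be kept. If patients with low volume also differ in their risk of complications, the retained groups differ in risk even when treatment does nothing. Because treating staff know the allocation, they can also influence which side of the threshold a control patient falls on.

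Achieved duration is likewise known only after randomisation. The rule could remove operations aborted, or deaths occurring, within 120 min, and death is a component of the primary endpoint. The algorithms do not set duration, however, so a route to different selection by arm is shown for volume only.

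At stake is the validity of the superiority claim, which rests on the upper 95% confidence limit of the odds ratio lying below 1.

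**Working it through.** **1. The plan's own figure.** Inputs from Sample size: 48% versus 33%, α = 0.05 (taken as two-sided), 80% power. With mean risk 0.405:

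n per arm = [1.96·√(2·0.405·0.595) + 0.8416·√(0.48·0.52 + 0.33·0.67)]² / 0.15² = (1.361 + 0.577)² / 0.0225 ≈ 167, so 334 in total, as stated.

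Six centres lose two patients each, which is 12. Then 334 × 1.10 + 12 = 379.4, or 380. The arithmetic of the sample size is not in question. The 10% is attributed to loss to follow-up, and the only other allowance is the first two patients per centre, so exclusions under the achieved-goal rule are not budgeted.

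**2. Order of events.** Expected values → enrolment and allocation → induction and start of the intervention → achieved duration and volume → exclusion. The exclusion therefore follows randomisation, and one of its criteria follows the start of treatment in a way that depends on the arm.

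**3. Reading of the rule.** The wording may mean that missing either goal leads to exclusion, or that only missing both does. The second reading removes fewer patients. Under both, achieved volume helps decide who stays.

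**4. Illustration of selection with no treatment effect.** The article gives no exclusion rates and no risk for the patients removed, so every rate here is an assumption. The number per arm is (380 − 12)/2 = 184, before any dropout. Let p = 0.40 be the risk in both arms, e the share removed and r the risk in those removed.

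- Retained risk = (p − e·r)/(1 − e)
- False-superiority rate ≈ Φ(−1.96 + RD/SE), where RD is control minus intervention risk among retained patients

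Worked case, 20% of control and 5% of intervention removed, r = 0.25:

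- Control: (0.40 − 0.05)/0.80 = 0.4375, n = 147.2
- Intervention: (0.40 − 0.0125)/0.95 = 0.4079, n = 174.8
- RD = 0.0296, SE = 0.0553, odds ratio = 0.89
- Φ(−1.96 + 0.536) = 7.7%, against a nominal 2.5%

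| Removed, control / intervention | Risk in removed | Odds ratio | False superiority |
|---|---|---|---|
| 10% / 10% | any | 1.00 | 2.5% |
| 5% / 2% | 25% | 0.98 | 3.1% |
| 10% / 5% | 30% | 0.98 | 3.2% |
| 20% / 5% | 25% | 0.89 | 7.7% |
| 25% / 5% | 20% | 0.80 | 16.7% |
| 5% / 20% | 25% | 1.13 | 0.6% |

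Over 10–25% removed from control, 5–10% from intervention and 20–30% risk in those removed, the odds ratio runs from 1.00 to 0.80 and the false-superiority rate from 2.5% to 16.7%. The last row reverses the removal rates and biases against the intervention. If the removed patients carry the average risk, there is no bias at any removal rates.

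**5. Same check at the protocol's control rate.** With 48% risk in both arms and 10% dropout, removing 15% of control and 5% of intervention patients at 25% risk leaves 52.1% versus 49.2%, an odds ratio of 0.89 and a false-superiority rate of 7.1%. The picture does not depend on choosing 40%.

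**6. Power.** (380 − 12) × 0.9 ≈ 331 evaluable patients give 79.7% power. Removing a further 5%, 10% or 15% (assumed) lowers it to 77.6%, 75.4% or 72.9%.

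**The case against.** **Few patients may miss the goals.** Entry requires open surgery expected to last at least 120 min with at least 2 l expected, so the rule may rarely apply. This stands as a limit on size: at 5% versus 2% removed the distortion is small. It does not justify the rule, because the removal rates are unknown in advance.

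**A reader might infer that the algorithm gives more fluid, so that the bias favours the intervention.** The article does not support this. Loading is conditional on PPV and CI at every stage, and the Discussion stresses that volume is given only when the individual CI target is not reached. What the text supports is that volume depends on the arm.

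**A reader might also infer that the duration criterion selects differently by arm.** Nothing shows this. Duration is a post-randomisation criterion that can touch the outcome, but it is not set by the algorithm.

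**The statistical analysis plan may define an all-randomised set.** It may, and it is not at hand. But this article states exclusion from the study, which is hard to reconcile with such a set, and no section returns these patients to the primary analysis. If exclusion also ends follow-up, a later plan could not recover their outcomes.

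**The 10% allowance may cover the loss.** It is assigned to loss to follow-up. In any case, extra numbers restore power and do not remove selection bias.

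**Conclusion.** The point holds and concerns a stated rule. Applied as written, it makes the primary comparison conditional on a variable that treatment can change, so randomisation no longer protects it. This holds whichever way the either/both ambiguity is resolved.

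The direction and size of the bias cannot be fixed from the article. On the assumed rates above, the false-superiority rate ranges from 0.6% (removal mainly from intervention) through 2.5% (no differential removal) to 16.7% (the most extreme case shown). These figures show sensitivity and are not estimates for this trial. Confidence is high for the structural flaw only. The threat to the primary result, set against a cheap remedy, makes this a change to require.

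**What to change.** Delete the exclusion on achieved duration and volume from Compliance/rate of loss to follow-up. State instead that every randomised, consenting patient, apart from the pre-declared first two per centre, is followed to day 28 and 6 months and analysed in the assigned arm in the primary model, whatever duration or volume was achieved. Keep the subset above 120 min and 2 l only as a sensitivity analysis, say whether one or both goals must be met, and report the number left out by arm and reason.

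The cost is a wording change and continued follow-up of patients already randomised. No treatment is altered and the sample size stays at 380. The downside is slight dilution of the effect by short or low-volume operations.

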### Sample size calculation and statistical analysis

#### Sample size

According to previous published data [24] assessing the impact of hemodynamic goal-directed therapy, we assume that the primary outcome will occur in 48% of the control group and in 33% of the intervention group. The null hypothesis of the study is that individualized, goal-directed therapy does not lead to a statistically significant difference in morbidity and mortality at day 28 after major abdominal surgery. Assuming in this null hypothesis (H0) that the two groups are not significantly different from each other at the significance level α = 0.05 with respect to the primary outcome, 334 patients are required to have an 80% chance of detecting a difference between the control group and the experimental group of 15%. Therefore, 167 patients per group would have to be enrolled into the study. Taking into account a dropout rate of about 10% and exclusion of the first two patients in every center, a number of *n* = 380 patients is necessary.

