### Study design

This is a prospective, multi-center, international, randomized controlled clinical trial in 380 patients scheduled for major abdominal surgery in six European centers having a large number of patients eligible for study inclusion (see Appendix). The study coordination will be conducted by a team of principle investigators (PI), [name], [name], [name], and [name], from the University Medical Center Hamburg-Eppendorf, Germany and from the Rostock University Medical Center, Germany.

The trial was designed in accordance with the fundamental principles established in the Declaration of Helsinki and within the requirements established by the German legislation in the field of biomedical research, the protection of personal data, and bioethics. The study was registered in January 2017 (received on 12 January 2017) at https://clinicaltrials.gov with the identification number NCT03021525. The study was approved by the Ethics Committee Giessen, Germany in February 2017 acting as the overall Ethical Review Board for this study (Additional file 1). Further, we can specify that all participating centers will obtain the approval from the local Ethical Review Board according to individual legislation regulations. Before inclusion into the study, written informed consent from the patient will be obtained (Additional file 2). See Additional file 3 for the Standard Protocol Items: Recommendations for Interventional Trials (SPIRIT) Checklist of the study protocol and Fig 1. for the adapted SPIRIT Figure.

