#### Primary analysis

For the primary endpoint “rate of moderate or severe postoperative complication or death within 28 days post surgery,” the fixed effect of treatment and the random effect of clinic and the treatment slope will be estimated by a binary logistic regression model. The resulting odds ratio with corresponding 95% confidence intervals (CI) and *p* values will be tabulated. Estimated marginal frequencies and their 95% CIs will be presented graphically. Superiority of the individualized hemodynamic therapy is considered established if the upper margin of the 95% CI of the corresponding odds ratio lies below 1.

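### The step from 334 to 380 slightly under-allows for a 10% loss, and it is unclear whether that 10% covers patients excluded after surgery for short duration or low volume

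*Protocol article*

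**What the plan says.** The Sample size section of the protocol article assumes the primary outcome in "48% of the control group and in 33% of the intervention group", "at the significance level α = 0.05 with respect to the primary outcome". From this it derives 334 patients, 167 per group, for 80% power. It then sets enrolment at 380, "Taking into account a dropout rate of about 10% and exclusion of the first two patients in every center". The Study design section places the trial in "major abdominal surgery in six European centers", so the training exclusion amounts to 12 patients.

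The section on compliance and loss to follow-up adds two statements. Patients whose operation does not exceed 120 minutes, or whose volume therapy does not exceed 2 litres, do not stay in: "they will be excluded from the study subsequently". On the allowance it says that "to reflect an unscheduled loss to follow-up an overall dropout rate of 10% is already included in the sample size calculation". Just before that, it describes loss to follow-up as unlikely.

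**The concern.** Two things do not fit together.

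First, raising a required number by 10% is not the same as allowing for the loss of 10% of those enrolled. The route to 380 appears to do the former.

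Second, actual operating time and actual volume are known only during or after surgery, whereas the intervention starts at induction of anaesthesia. The exclusion therefore removes patients who have already been allocated and treated. The sample-size section lists two deductions, dropout and training patients, and this is neither by name. The sentence on the 10% gives unscheduled loss to follow-up as its reason, and a removal that the protocol itself prescribes is not obviously that.

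At stake is whether the stated 80% power can be relied on. There is also a question of selection: the algorithms in the intervention arm direct fluid boluses of 500 ml, so allocation can influence whether a patient passes the 2-litre limit.

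**Working it through.** **Inputs.** Event rates of 48% and 33%, α = 0.05, 80% power, 334 evaluable, about 10% dropout and 380 enrolled (Sample size); 1:1 allocation (Randomization); six centres (Study design); two training patients per centre (Documentation and data acquisition). Sidedness is not stated with the calculation. Two-sided is inferred from the decision rule, which declares superiority "if the upper margin of the 95% CI of the corresponding odds ratio lies below 1", and from the fact that it reproduces 334 (one-sided gives 264). No rate is given for the exclusion after surgery.

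**Reproducing 334.** Pooled two-proportion formula, no continuity correction, mean rate (0.48 + 0.33)/2 = 0.405:

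- 1.960 × √(2 × 0.405 × 0.595) = 1.3607
- 0.8416 × √(0.48 × 0.52 + 0.33 × 0.67) = 0.8416 × 0.6861 = 0.5774
- n per arm = (1.3607 + 0.5774)² / 0.15² = 166.94, so 167 per arm and 334 in total. This matches.

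**Reproducing 380.** 334 × 1.10 = 367.4, rounded up to 368; 368 + 6 × 2 = 380. This matches exactly, so the plan multiplied by 1.10.

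**Allowing for a true 10% loss.** 334 / 0.90 = 371.1, rounded up to 372; 372 + 12 = 384.

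**What 380 delivers.** Non-training patients: 380 − 12 = 368. Power with n per arm is Φ[(0.15√n − 1.3607) / 0.6861].

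- No loss: 368 evaluable, power 83.7%.
- 10% loss: 368 × 0.90 = 331.2 evaluable, power 79.7%.
- Break-even: 1 − 334/368 = 9.2%, which leaves 334 and 80.0%.

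**Adding the exclusion after surgery.** The exclusion rates, and the 3% loss, are assumptions.

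| Reading of the 10% | Excluded | Lost to follow-up | Evaluable | Power |
|---|---|---|---|---|
| Follow-up only, fully used | 2% | 10% | 368 × 0.98 × 0.90 = 325 | 78.9% |
| Follow-up only, fully used | 5% | 10% | 368 × 0.95 × 0.90 = 315 | 77.6% |
| Follow-up only, fully used | 10% | 10% | 368 × 0.90 × 0.90 = 298 | 75.4% |
| Covers both losses | 5% | 3% | 368 × 0.95 × 0.97 = 339 | 80.6% |

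At 5% excluded, 380 still leaves 334 as long as follow-up loss stays at or below 1 − 334/349.6 = 4.5%.

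**The case against.** The strongest reply is that nothing material is wrong. The plan says about 10%, and 9.2% fits that description and leaves exactly 334. Even at 10.0% the gap is 3 patients and 0.3 power points, which is trivial beside the uncertainty in the assumed event rates. That stands: the multiplication slip alone would not justify changing the enrolment.

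The reply also disposes of three stronger readings that a reader might infer:

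- *That exclusions after randomisation are not budgeted at all.* They are in part: the first two patients per centre are named and counted.
- *That 80% is the most the trial can achieve.* It is not. Power is above 80% whenever total loss is below 9.2%, and the article itself expects little loss to follow-up.
- *That power is really in the mid-70s.* This needs an exclusion rate that the document does not give, added to a full 10% follow-up loss. The article calls the 10% an overall rate, in the same paragraph as the exclusion rule, and eligibility already screens on expected duration and volume.

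It can also be said that a condensed article need not break down its dropout allowance. That is fair for a breakdown as such. But the article itself fixes the enrolment figure, the allowance and the removal rule, and it gives the allowance a reason that does not clearly include the removals. That ambiguity stands.

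**Conclusion.** The concern holds in a limited form. The base of 334 is right and the training patients are budgeted. The dropout step is a minor arithmetical slip: at exactly 10% loss the yield is 331 evaluable and 79.7% power, not 334 and 80.0%.

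The more useful point is the unresolved exclusion of treated patients for short surgery or low volume. Depending on whether the 10% includes it, the same 380 patients give about 80% power or, at assumed exclusion rates of 5% to 10% on top of a full 10% loss, 77.6% to 75.4%. The documents do not say which reading is meant, so they do not support a claim that the trial is underpowered or that more patients must be enrolled.

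These figures rest on a two-sided 5% comparison of two proportions at the plan's own event rates, with equal arms after losses and no allowance for differences between centres. The plan's 334 is reproduced on the same basis.

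**What to change.** 1. Keep every randomised non-training patient in the primary analysis, including those whose surgery was short or whose volume was low. No further allowance is then needed, and nobody is selected on a volume that the allocated algorithm can change. Amend the exclusion sentence in the section on compliance and loss to follow-up to match.
2. Restate the sample-size sentence along these lines: 380 enrolled, less 12 training patients, gives 331 evaluable patients and 79.7% power at 10% loss to follow-up, and 334 patients and 80.0% power at 9.2%.
3. If the investigators want a result in patients who met both limits, keep a per-protocol analysis as a sensitivity analysis.

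The cost is wording only, with no extra enrolment. The stated power is slightly less favourable. The primary analysis will include some patients with limited surgical exposure, in whom the treatment effect may be smaller than assumed; the sensitivity analysis is there to show whether that matters.
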